### Outcomes

2.7

Cardiac function: Color Doppler ultrasonography (GE-VIVID7, US) was used before and after treatment and during follow-up time to detect patient's left ventricular end-diastolic diameter, left ventricular end-systolic diameter, and LVEF.Blood lipid levels: Fasting vein blood was collected in the morning before and after treatment and during follow-up time, and automatic biochemical analyzer (HITEC-7100, Japan) was used to detect blood lipid indexes of the patients, including total cholesterol; triacylglycerol; low density lipoprotein cholesterol; high-density lipoprotein cholesterol.The number of weekly attacks of angina pectoris; total amount of nitroglycerin tablets taken during the study period.

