### Study design

2.1

This is a prospective, randomized, double-blind, placebo-controlled study of the effects of Danhong injection on cardiac function and lipid profile in patients with angina pectoris of coronary heart disease. Participants will be randomly divided into treatment group and control group, the treatment group will receive Danhong injection treatment, and the control group will receive placebo treatment. The patients will be followed up for 3 months after 14 days of continuous treatment. Flow diagram is shown in Figure 1, study schedule is shown in Table 1. This protocol followed the latest Consolidated Standards of Reporting Trials 2017 and Standard Protocol Items: Recommendations for Interventional Trials 2013 statement.

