**Figure 1 F1:**
[figure not shown]
Flow diagram of this clinical trial.

**Table 1 T1:** Study schedule.

	Screening period	Treatment period		Follow-up		
--Project Stage	Baseline	1-wk	2-wk	1-mo	2-mo	3-mo
Record fill	√					
Fulfill inclusion criteria and exclusion criteria	√					
Sign informed consent	√					
Random allocation	√					
Treatment	√	√	√			
Effectiveness observation						
Cardiac function	√		√			√
Blood lipid levels	√		√			√
The number of angina attacks per week	√	√	√	√	√	√
Total amount of nitroglycerin tablets	√		√			√
Safety evaluation						
Blood test and urinalysis	√		√			√
Liver and kidney function	√		√			√
Record of adverse event		√	√	√	√	√

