#### Shedding criteria and management

2.3.4

Patients who appear severe adverse events or other complications and special physiological changes. The trial should be stopped and corresponding treatment should be given according to the judgment of the investigator;If the subject's condition does not improve or even deteriorate to a certain extent within a certain period of time, although the required follow-up had not been completed, the subject should be withdrawn from the study and received other effective treatments in order to protect the subject;Patients who have poor compliance, change medications or add non-prescribed medications, which may affect the result of the study;Patients who are unwilling or impossible to continue the clinical trial for any reason, and suspend the test by requesting the investigator to withdraw from the test;Patients who are misdiagnosed, or accidentally included without meeting the inclusion and exclusion criteria.

For patients who dropped out of the trial or lost to follow-up, researchers should take active measures to complete the last test as far as possible, so as to analyze its efficacy and safety, and take corresponding treatment measures. All shedding cases should be recorded on the case report form (CRF), and filled in the cause.

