### Intervention measures

2.6

According to *2014 American College of Cardiology/American Heart Association Guidelines for the Diagnosis and Treatment of Non-ST-Segment Acute Coronary Syndrome*, all patients would receive dual antiplatelet therapy (aspirin 100 mg/d +clopidogrel 75 mg/d) and anticoagulant therapy (unfractionated heparin). And they would also receive statins, angiotensin converting enzyme inhibitors, beta-blockers, and nitrates according to the guidelines.^[18]^ All of these basic treatments will be detailed on the patient's medical record and CRF.

The treatment group was treated with Danhong Injection (Danhong Pharmaceutical Co., Ltd., Shandong, China), 40 ml/d combined with 0.9% normal saline, 250 ml/d intravenously, and the control group was treated with placebo (0.9% normal saline), 40 ml/d, combined with 0.9% normal saline, 250 ml/d, intravenously. All patients received standard treatment for 14 days.

When angina attacks, patients were instructed to take nitroglycerin tablets (Yimin Pharmaceutical Co., Ltd., Beijing, China), 0.5 mg/time, repeated every 5 minutes until angina relieved. Timing and dosage would be recorded in detail on the Case Report Form.

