### Statistical analysis

2.10

Efficacy evaluation will be determined by full analysis set and per-protocol set, and safety evaluation will be based on safety set. Statistical evaluation of full analysis set will follow intent-to-treat principles. Last observation carried forward method was used to estimate missing values of major variables. The collected data were statistically analyzed by SPSS 22.0 software. Chi-square test was used for enumeration data; mean value ± standard deviation ($\bar{\text{x}}$ ± S) was used for measurement data, independent sample *t* test was used for normal distribution, and Mann-Whitney *U* test was used for skewed distribution. When *P* < .05, the difference was considered statistically significant.

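### Nitroglycerin use is defined as one raw total over the whole study, so early withdrawal counts as low use, and the definition does not fit the assessment times in Table 1

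*Protocol article*

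**What the plan says.** - **Outcome definition (protocol article, section 2.7).** The outcome is "total amount of nitroglycerin tablets taken during the study period". Beside it stands the other symptom outcome, "The number of weekly attacks of angina pectoris", which is expressed per unit of time.
- **Study length (section 2.1).** "The patients will be followed up for 3 months after 14 days of continuous treatment".
- **Schedule (Table 1).** The row "Total amount of nitroglycerin tablets" is ticked at baseline, 2 weeks and 3 months.
- **Recording (section 2.6).** For nitroglycerin taken during attacks, "Timing and dosage would be recorded in detail on the Case Report Form".
- **Withdrawal (section 2.3.4).** For patients who fail to improve or who get worse, the rule is that "although the required follow-up had not been completed, the subject should be withdrawn from the study". For those who leave, researchers are asked to try to obtain a last assessment.
- **Analysis (section 2.10).** "Statistical evaluation of full analysis set will follow intent-to-treat principles". A per-protocol analysis is also planned. Measurement data are compared by t test or Mann-Whitney test. "Last observation carried forward method was used to estimate missing values of major variables"; the major variables are not listed.

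**The concern.** A total can be compared between patients only if they are observed for the same length of time. Here they will not be, because the protocol provides for early withdrawal and one of its grounds is a poor clinical course. Patients withdrawn on that ground are plausibly heavier users of nitroglycerin, yet their totals stop growing when they leave. Neither planned test takes observation time into account. An arm with more early failures could therefore appear to need less nitroglycerin.

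Two further problems come from the same definition. First, a total for the study period has no value at baseline, and a single whole-study total has no use for a separate 2-week assessment, so section 2.7 and Table 1 describe different outcomes. Second, the total merges a short treatment period with a much longer period after treatment, so an effect present only during infusion would be hard to see.

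This is one of only two symptom outcomes in the trial.

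**Working it through.** The protocol gives no numerical figure for nitroglycerin use, so there is none to reproduce. Its planned drop-out of 10% (section 2.4) is used below for context; its inflation is right (49/0.90 = 54.4, rounded up to 55).

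**Inputs.** Treatment lasts 14 days and follow-up 3 months (section 2.1). I take 3 months as 91 days, with a range of 84 to 92. Weekly use, withdrawal gaps and exit times are not in the protocol and are assumptions.

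**1. Off-treatment share of the total as section 2.7 words it.** Share = follow-up days / (14 + follow-up days).

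| Follow-up days | Share |
|---|---|
| 84 | 84/98 = 85.7% |
| 90 | 90/104 = 86.5% |
| 91 | 91/105 = 86.7% |
| 92 | 92/106 = 86.8% |

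**2. What an early leaver scores.** At equal weekly use, a patient leaving at day 14 has 14/105 = 13.3% of a completer's total. At an assumed 3 tablets per week, the completer totals 3 × 15 = 45 and the leaver 3 × 2 = 6. Both have a rate of 3 per week.

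**3. Effect on the comparison of means, with equal true use in both arms.** Fall in an arm's mean total = extra proportion withdrawn × mean days lost / 105. Exits at day 14 lose 91 days; exits spread evenly over follow-up lose 45.5 days on average.

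| Extra withdrawal, against none in the other arm | All at day 14 | Spread over follow-up |
|---|---|---|
| 5 points | 0.05 × 91/105 = 4.3% | 0.05 × 45.5/105 = 2.2% |
| 10 points | 0.10 × 91/105 = 8.7% | 0.10 × 45.5/105 = 4.3% |

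The same 10-point gap around the planned 10%, as 15% against 5% at day 14, gives mean totals of 0.870 and 0.957 of full exposure, a ratio of 0.91. With 10% in each arm the ratio is 1.00.

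**4. Dilution.** If treatment halved use during infusion with no carry-over (assumption), the whole-study total would fall by 0.5 × 14/105 = 6.7%. A 30% reduction during infusion would appear as 0.3 × 14/105 = 4.0%.

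**5. If last observation carried forward applies to this outcome.** Carrying a cumulative total forward sets use after exit to zero. Carrying the 2-week total into a separate follow-up slot puts 14 days of use in place of about 91. Neither repairs the total. If nothing is carried forward and recorded tablets are simply summed, the total still stops at exit.

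**The case against.** Several objections have force.

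- **The 87% depends on section 2.7.** Table 1 schedules a 2-week value and section 2.6 has each intake dated, so an on-treatment total can be derived. A reader might infer that the trial has no on-treatment measure of nitroglycerin use. The protocol does not support that; it supports only that the outcome text defines none and that the two places disagree.
- **Carrying forward is limited to unlisted major variables.** A reader might infer that tablet counts will be carried forward. Nothing says so. The exposure-time problem does not need it (step 5).
- **Bias between arms needs unequal withdrawal.** The protocol predicts no gap. A reader might infer that the definition favours Danhong; it favours whichever arm loses more patients, and neither if withdrawal is alike. The percentages also describe means and do not carry over to a Mann-Whitney test.
- **Including follow-up is deliberate.** The protocol states an interest in longer-term efficacy, and measuring use after treatment is legitimate. The fault is in merging the two periods without a denominator.
- **Safeguards exist.** There is a last assessment for leavers, a per-protocol analysis, and weekly angina attacks as a companion outcome. A last assessment made at exit does not lengthen the time over which tablets are counted, and a per-protocol analysis leaves the full-analysis-set comparison as it was.
- **The choice of model may belong in an analysis plan that is not shown.** I agree. The definition of the outcome, however, is stated in the article.

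**Conclusion.** The point holds in this form. Section 2.7 fixes an unnormalised whole-study total that does not match Table 1. Combined with withdrawal for poor course and the full analysis set, it counts early exit as low use.

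For an individual, the distortion is large: about 13% of a completer's total for exit at day 14 at equal weekly use. Between arms it is conditional. A 10-point withdrawal gap lowers the mean by about 4% to 9%, depending on when exits occur and assuming equal use. There is no bias in means if withdrawal is equal in amount and timing and unrelated to use. If leavers are the heavier users, the distortion for a given gap is larger.

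The dilution (6.7% for a halving during infusion) assumes no carry-over and applies to section 2.7's wording only. The sample size rests on ejection fraction and is unaffected. This should be corrected, but it does not threaten the trial as a whole.

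**What to change.** 1. Reconcile section 2.7 with Table 1, so that both name the same outcome at the same times.
2. Define the outcome as nitroglycerin tablets per week of observation, reported separately for the 14-day treatment period and the 3-month follow-up.
3. Define the baseline value as use in a fixed window before randomization.
4. Compare arms on a basis that accounts for observed time. A count model with log observed time as offset is one suitable choice, not the only one.
5. If last observation carried forward is meant to cover this outcome, state that cumulative tablet counts are not carried forward.

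The cost is mainly wording and slightly more analysis. Intake is already to be recorded with its timing and dosage, and the 2-week assessment is already scheduled; the baseline window must be fixed before enrolment if it is to be collected consistently. The drawback is that rates from patients observed only briefly are noisier, which a model with a time offset allows for by giving them less weight.

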### Safety evaluation

2.8

Blood routine tests, urine routine tests, liver function(ALT, AST, DBIL, IBIL, ALP, γ-GT), renal function (BUN, Scr) and ECG were performed at baseline and after treatment to evaluate the safety of treatment. Patients would be asked to report any abnormal reactions to the researchers during the study. Details of all adverse events would be recorded in CRF, including the time, extent and duration of occurrence, suspected reasons, effective measures, and outcomes. After treatment, the incidence of adverse reactions in the 2 groups was analyzed.

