**Methods::**

This is a prospective, randomized, double-blind, placebo-controlled trial to study the effects of Danhong injection on cardiac function and lipid profile in patients with angina pectoris of coronary heart disease. Participants will be randomly divided into treatment group and control group. The treatment group will be treated with Danhong injection and the control group will be treated with placebo under basic treatment according to recommended guideline, and followed up for 3 months after 14 consecutive days of treatment. Outcomes include: cardiac function (left ventricular end-diastolic diameter); left ventricular end-systolic diameter; left ventricular ejection fraction, blood lipid levels (total cholesterol; triacylglycerol; low density lipoprotein cholesterol; high density lipoprotein cholesterol), the number of angina attacks per week, total amount of nitroglycerin tablets, and adverse reactions.

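### Section 2.8 records all adverse events but compares only adverse reactions between arms, and it disagrees with Table 1 on ECG and 3-month laboratory tests

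*Protocol article*

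**What the plan says.** On recording, section 2.8 is broad: "Details of all adverse events would be recorded in CRF, including the time, extent and duration of occurrence, suspected reasons, effective measures, and outcomes". On analysis, it is narrower: "After treatment, the incidence of adverse reactions in the 2 groups was analyzed". No other between-arm safety comparison is stated. The abstract uses the narrower term too, ending its list of outcomes with "total amount of nitroglycerin tablets, and adverse reactions". Section 2.10 bases the safety evaluation on the safety set and says nothing about which events are counted.

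On timing, section 2.8 says of the laboratory tests and the ECG: "renal function (BUN, Scr) and ECG were performed at baseline and after treatment to evaluate the safety of treatment". In Table 1, the row "Record of adverse event" is ticked at 1 and 2 weeks and at 1, 2 and 3 months. The rows for blood and urine tests and for liver and kidney function are ticked at baseline, 2 weeks and 3 months. Table 1 has no ECG row.

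**The concern.** An adverse event is anything untoward that happens. An adverse reaction, in the usual sense, is an event that someone has judged to be caused by a drug. A randomized, placebo-controlled, blinded design lets the arms be compared on all events, with no need for a causality judgement on each patient. Restricting the comparison to reactions brings that judgement back, and the article gives no rule for making it.

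This matters more than usual here. Section 2.6 gives every patient aspirin, clopidogrel and unfractionated heparin. The Introduction lists an anticoagulant effect among the pharmacological actions of the study drug, and section 2.3.3 excludes patients at raised risk of bleeding. For any bleed there is a ready alternative cause in both arms. An added contribution from the study drug would show most clearly in the count of all events, which section 2.8 does not say will be compared.

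The schedule mismatch is a separate matter. It bears on which safety data are collected, not on how they are analysed.

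**Working it through.** **1. Recorded against compared.** Within section 2.8, the recording sentence covers all events and the comparison sentence covers reactions. The abstract repeats the narrower term, so it is not confined to one sentence. A suspected cause is recorded for each event, so the data needed to filter by attribution will exist, although no filter is described.

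**2. Effect of a filter on counts.** The plan gives no safety rates, so there is no figure of its own to reproduce. The one input from the document is the 55 patients per arm in section 2.4. The event rates and retained fractions below are assumptions for illustration.

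- True rates of any event: p1 = 0.10 (placebo) and p2 = 0.20 (treated).
- A fraction f of events is classed as reactions, the same in both arms because attribution is made blind.
- Expected counts are 55·f·p1 and 55·f·p2. The ratio stays at f·p2 / f·p1 = 2 for every f.
- Power (two-sided 5%, normal approximation) = Φ{ [ d − 1.96·√(2·p̄(1−p̄)/n) ] / √( [p1(1−p1) + p2(1−p2)]/n ) }, with n = 55, d the difference in rates and p̄ their mean. For f below 1, the rates f·p1 and f·p2 replace p1 and p2 throughout.

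| f | Rates | Expected counts | Power |
|---|---|---|---|
| 1 | 10% v 20% | 5.5 v 11 | about 31% |
| 0.5 | 5% v 10% | 2.75 v 5.5 | about 17% |
| 0.25 | 2.5% v 5% | 1.375 v 2.75 | about 10% |

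For f = 1: (0.10 − 1.96 × 0.0681) / 0.0674 = −0.496, and Φ(−0.496) = 0.31.

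Even unfiltered, a doubling is not reliably detected. Counts of 5 v 11 of 55 give an uncorrected chi-square P of about 0.10, and 6 v 11 give about 0.19. The filter reduces information that is already scarce.

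**3. Section 2.8 against Table 1.**

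| Item | Section 2.8 | Table 1 |
|---|---|---|
| ECG as a safety test | Baseline and after treatment | No row |
| Blood, urine, liver and kidney tests at 3 months | Not named | Ticked |

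The post-treatment wording in section 2.8 might be stretched to cover 3 months. Section 2.7 argues against that. For cardiac function and lipids, which Table 1 also ticks at baseline, 2 weeks and 3 months, section 2.7 names the follow-up period in addition to the measurement after treatment. The authors thus use separate words for the two times, and section 2.8 has only one of them.

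**The case against.** The strongest reply is that the authors use the terms loosely. Section 2.8 moves between abnormal reactions, adverse events and adverse reactions within a few sentences. It defines no reaction, sets no causality scale and does not say that other events are excluded. The suspected cause is one item in a list of recorded details, not an inclusion rule. This is fair: the narrow reading is the usual technical one, but it is not certain to be the intended one. If it is not intended, the correction is a single word, and it is still needed because the text as written permits the narrower analysis.

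Three stronger readings are tempting and are not supported.

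- *Bleeding will usually be attributed to background drugs and hidden.* Nothing in the article says how events will be attributed. It supports only that another cause is readily available.
- *The filter favours the study drug.* Section 2.5 keeps patients and the principal investigator unaware of allocation and covers the infusion bottles. If that holds, attribution should be similar in both arms and the ratio is preserved, as shown above. The cost is in counts and precision. Nor can a missed doubling be put down mainly to the wording, since 55 per arm would probably miss it in any case.
- *Sites working from Table 1 would collect no ECG safety data.* Section 2.8 requires the ECG expressly, and a missing row does not cancel that. Eligibility under section 2.3.2 also refers to ECG changes, so a baseline tracing may exist anyway. The exposed item is the post-treatment ECG, which has no prompt in the schedule.

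It is also fair that effect measures, confidence intervals and table layouts belong in an analysis plan. Their absence from the article is not part of this point.

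**Conclusion.** The point holds in a limited form. The only stated between-arm safety comparison is, in its usual sense, restricted to events judged drug-related, although all events are recorded. No event is lost from the record, since events stay on the case report form through 3 months; what is at risk is their inclusion in the comparison. With blinding intact, the consequence is fewer events and less precision, not a bias towards either arm. On the assumed rates, power falls from about 31% to 17% or 10% if half or a quarter of events count as reactions. Those figures rest on assumed rates and on equal attribution in both arms, and show direction and rough scale only.

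The contradictions between section 2.8 and Table 1 on the ECG and the 3-month laboratory tests do not depend on how the word reaction is read. Efficacy conclusions are not touched by either part. The changes should be made because they cost little and the safety conclusion depends on them.

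**What to change.** In section 2.8, state that the between-arm comparison is the incidence of all recorded adverse events in the safety set, through 3 months and regardless of attribution, with serious events and bleeding events identified. Keep adverse reactions as a secondary summary, and bring the abstract into line. The events are already on the case report form, so the cost is wording and a few extra summaries. The one downside is that headline safety rates will be higher than for reactions alone.

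Separately, reconcile section 2.8 with Table 1 on the ECG and on the 3-month blood, urine, liver and kidney tests. The sponsor should decide which schedule is intended and state it identically in both places, so that the intended safety data are collected. This is an editorial change if made before data collection.

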### Data management and quality control

2.9

Any modifications or changes to the protocol will be re-approved through a formal process by the Hospital Ethics Committee. Independent clinical research assistants will periodically review research progress. Study data will be collected and recorded in CRF by trained investigators. To ensure reliability of data, personal information about potential and registered participants will be collected, shared and kept in a separate repository to protect confidentiality before, during, and after the trial. Access to the database will be restricted to the researchers in the research team. Participants’ information will not be open or shared without their written permission.

